| Domain                                                                       | Strategy                                                                                                                                                                                                                                                                                                                                                                                                             |
| Actor                                                                               | 
 
Non- punitive Mentor who provides training, mentorship and coaching
 
                                                                                                                                                                                                                                                                                                       |
| Action                                                                              | 
 
Provides training and ongoing mentorship on PCC to HCW
 
Supports use of client experience data
 
Incentives for best performing facilities
 
                                                                                                                                                                                                                 |
| Action Target                                                                       | 
 
All Lay and Professional HCWs trained in PCC
 
All cleaners and security guards trained in PCC
 

 
                                                                                                                                                                                                                                                           |

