**Training and Facilitation:** The PCC intervention started with a two-day interactive training program that focused on strategies to improve the quality of interactions, included modules on PCC principles, client-provider communication, and stress management. Trainings were held outside the facility and targeted all HCWs (i.e., lay health workers, counsellors, medical officers, clinical officers, nurses, pharmacists, data managers) as well as facility support staff (e.g., security guards, cleaners), recognizing that interactions with any facility staff could influence the client experience and that HCWs commonly transfer between departments. After training was complete, study clinical mentors (i.e., 14 nurses and clinical officers trained in practice facilitation for person-centered care that oversaw 2-3 facilities each) provided ongoing support at facilities through approximately twice weekly mentorship facility visits throughout the intervention. Mentorship visits involved short lectures, role plays, and facilitated group discussion sessions that were tailored based on mentor assessment of facility needs and were delivered in a supportive manner that recognized the challenges faced by HCWs. During COVID-19 periods, trainings occurred in smaller groups (e.g., 5-10 HCWs rather than 40 HCW at a time).

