## **Procedures for Event adjudication for treatment failure**

Five adjudicators independently reviewed all EMR records among individuals who did not have a documented viral load during the study interval of interest. We used an Extended Outcome and Investigation Classification (EOIC) ascertainment process (Supplementary Fig 3) which included intensive tracing and adjudicated for outcomes based on their prior viral load history and retention in care history.

Individuals with a documented suppressed viral load during the study outcome window (i.e., 11 to 19 months) were classified as “Definite success”. Individuals with a documented unsuppressed viral load or clear documentation of not taking medications as “Definite failure.” Individuals who did not have a documented viral load during the study window were classified as either “Probable success” or “Probable failure” based on their prior viral load history, retention in care history (e.g., missed visits, running out of medications based on pharmacy records), and evidence of care based on tracing based on the adjudication process by 5 team members. For example, if at 15 after randomization, no viral load outcomes were obtained, and a team found the clients who reported no care and stopping treatment, the client would be classified as a definite failure. On the other hand, if the client reported continuing in care and taking medications at an outside facility, even if it is one were not able to obtain viral load results from, and the visit history indicates continuous engagement, the client would be classified as probable success.

[figure not shown]

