## Outcome ascertainment process

If a patient does not have a viral load recorded in the interval of interest, we used an extended outcome ascertainment (EOIC) process. The EOIC process includes: intensive tracing to ascertain vital status and care status (informants to assess patient outcomes can include health care workers, community members, family and others). Information used all information about the patient and was adjudicated by a 7-team group (including physicians, nurses, and mentors) to assess whether individuals have evidence of being actively engaged in HIV care.

Based on EOIC, adjudication process, and viral loads; the primary outcome will be further characterized as:

1. "Definite success"
2. "Probable success"
3. "Probable failure"
4. "Definite failure"

Individuals with a documented suppressed viral load during the study outcome window (i.e., 11 to 19 months) are classified as "Define success". Individuals with a documented unsuppressed viral load or clear documentation of not taking medications as "Definite failure." Individuals who did not have a documented viral load during the study window were classified as either "Probable success" or "Probable failure" based on their prior viral load history, retention in care history (e.g., missed visits, running out of medications based on pharmacy records), and evidence of care based on tracing based on the adjudication process by 7 team members. For example if at 15 after randomization, no viral load outcomes were obtained, and a team found the patients who reported no care and stopping treatment, the patient would be classified as a definite failure. On the other hand, if the patient reported continuing in care and taking medications at an outside facility, even if it is one were not able to obtain viral load results from, and the visit history indicates continuous engagement, the patient would be classified as probable success.

Flowchart: Treatment outcome adjudication algorithm

[figure not shown]

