## Analysis

**Primary outcome:** The primary outcome is treatment failure (as defined above) at 15 months. Those assessed as “Definite success” and “Probable Success” based on viral load results and EOIC processes will be treated as successes. “Probable Failure” & “Definite failure” are defined as a failure.

**Primary analysis of primary outcome:** We plan use of mixed effects logistic regression, accounting for clustering at the facility-level using random effects, to assess the effect of the PCC intervention on treatment success. The main exposure will be exposure to the PCC intervention. To account for potential imbalances due to cluster randomization at baseline and also increase precision, we will adjust for baseline viral suppression (new ART will be assumed to be unsuppressed), care status at enrollment (in care, new ART, LTFU), sex, age, time in care, and randomization strata (initial cluster randomization stratified by facility size and viral load coverage based on programmatic data). Facility clustering will be address through random effects. We will consider including the following potential confounders due to imbalance in randomization: WHO severity groups, marital status and education. We will use standard model diagnostic procedures and consider alternate specifications as needed if we face challenges with standard statistical issues such as model convergence or overfitting. We will use marginal estimation commands to report absolute and relative risk differences under treatment versus control conditions.

In addition to the overall analysis, we will perform stratified analyses to assess changes specifically across:

- Care status (in care, new ART, LTFU) at onset of enrollment
- Baseline viral suppression
- Sex
- Age (<25, 25-44, >45 years)

- Advanced HIV Disease at enrollment in care (WHO Stage 3 or 4, or CD4<200)
- Clinic size and type
- We may assess composite subgroups of age, sex, care status, and suppression status (e.g., Male <25 years old, LTFU not suppressed at baseline) if amenable based on sample sizes.

We will not perform analyses with less than 75 participants.

Sensitivity Analysis of primary outcome: We will perform several sensitivity analyses to ensure the robustness of our results

- Treat “Definite success” as success and everything else as failure (i.e., “probable success” equals failure)
- Treat “probable success” and “probable failure” as missing (i.e., only include definite results)

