## **4.0 – Secondary Outcome – Patient Experience**

### **Trained exit client (TEC) survey data**

For TEC analysis, the measure of interest was onl

y collected in waves 2, 3, and 4. In wave 1 (first 6 months), all facilities adhered to the standard of care. This was to ensure that all waves included at least one baseline period where they were in the control state to increase power. This was an open-label trial in which HCW/ facilities and patients were unblinded to the intervention itself. However, the timing of the transition was only revealed to facilities during sensitization at time zero. Facilities were then reminded of the transition two weeks before the intervention was introduced.

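### The group that adjudicates the primary outcome includes mentors, who deliver the intervention, and no masking to facility, wave or arm is specified

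*Combined protocol and SAP*

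**What the plan says.** SAP 3.0, Outcome ascertainment process, sends patients without a viral load at 11 to 19 months to intensive tracing and then to a panel. Their outcomes are "adjudicated by a 7-team group (including physicians, nurses, and mentors"). On what the panel sees, the text reads "Information used all information about the patient". Probable calls rest on earlier viral loads, retention history and tracing evidence. Under Analysis in the same section, definite and probable successes "based on viral load results and EOIC processes will be treated as successes", and both kinds of failure count as failures.

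The appendix, Intervention Description, names the mentor as the actor in its strategy table. It describes "study clinical mentors (i.e., 14 nurses and clinical officers trained in practice facilitation for person-centered care that oversaw 2-3 facilities each").

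The appendix section on event adjudication describes the panel differently: "Five adjudicators independently reviewed all EMR records among individuals who did not have a documented viral load during the study interval of interest". It does not say who the five were.

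The only statement on blinding is in SAP 4.0, on the exit-client survey: "This was an open-label trial in which HCW/ facilities and patients were unblinded to the intervention itself". It does not mention adjudicators. Protocol 8.7.2.2, on treatment failure, describes tracing but names no committee and no masking.

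**The concern.** In a parallel comparison of Wave 1 with Wave 4, the clinic determines the arm. A panel member who sees the clinic name, the calendar dates together with the clinic, or a mentor's notes can work out the arm. Mentors have a stake in the result. A probable call weighs several kinds of indirect evidence, and that leaves room for a small, unintended lean. A lean that differs by arm passes straight into the treatment effect and does not average out with more patients.

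The cases judged also differ between arms. Among patients who needed adjudication, Table S11 gives silent transfers as 15/73 (20.6%) in control and 7/77 (9.1%) in intervention (p=0.044). Reported care at an outside clinic with no viral load is the SAP's own example of a call the panel must make. This cuts both ways: a different case mix makes consistent judgement matter more, and it could also explain a difference in success share without any bias.

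**Working it through.** **Inputs**
- Table S10 (no viral load, adjudicated), control / intervention: 73 / 77 patients; definite failure 14 / 16; probable failure 32 / 27; probable success 27 / 34; definite success 0 / 0.
- Table S12 (missing viral load counted as failure): successes 352/453 and 368/480.
- SAP 3.0 sample size: design target of 10.7 points.
- Assumption: the Table S12 successes are exactly the definite successes. Its title and the zero row in Table S10 imply this.

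**Reproducing the plan's figure.** Pearson chi-square on the three non-empty rows of Table S10 gives 1.25 on 2 df, p=0.534. The table states 0.53.

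**Share of outcomes that rest on judgement**
- Adjudicated: 73 + 77 = 150; 150/933 = 16.1%.
- Probable calls: control 32 + 27 = 59, intervention 27 + 34 = 61; 120/933 = 12.9%.

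**Direction of the probable calls**
- Called success: control 27/59 = 45.8%, intervention 34/61 = 55.7%; difference 10.0 points.
- Chi-square = 120 × (27×27 − 34×32)² / (59×61×61×59) = 1.19 on 1 df, p=0.27. This ignores clustering.

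**Effect on the crude risk difference (intervention minus control)**

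| Handling of probable calls | Control | Intervention | Difference (points) |
|---|---|---|---|
| As adjudicated | (352+27)/453 = 83.7% | (368+34)/480 = 83.8% | +0.1 |
| All counted as failure | 352/453 = 77.7% | 368/480 = 76.7% | -1.0 |
| Excluded (definite only) | 352/(453−59) = 89.3% | 368/(480−61) = 87.8% | -1.5 |
| Intervention given control's success share | 83.7% | (368+61×27/59)/480 = 82.5% | -1.2 |

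**How far judgement could move it**
- One call changed: 1/480 = 0.21 points in intervention, 1/453 = 0.22 in control. Ten calls in one arm: 2.1 to 2.2 points.
- Logical limits, with every probable call going one way in one arm and the other way in the other: (368+61)/480 − 352/453 = +11.7, and 368/480 − (352+59)/453 = -14.1. These limits are as wide as the 10.7-point target, but they are bounds and not plausible values.

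**What the planned sensitivity analyses cover**
- Only definite success counts as success: this requires a documented suppressed viral load, so panel judgement cannot change it. Table S12 reports an adjusted difference of 0.1 (-9.2 to 9.3), p=0.99.
- Definite results only: this still contains 14 + 16 = 30 definite failures that had no viral load and came through adjudication.

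**The case against.** The strongest answer is that the plan already contains a test immune to this bias. Counting only documented suppression as success removes the panel from the result. That analysis was pre-specified, is reported in Table S12, and shows no difference. This stands, and it is the main reason the point is not more serious. It does not settle everything. It counts every patient without a viral load as a failure, so it answers a different question from the primary outcome, and its interval is wide.

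Second, the appendix says that review was independent, and both documents refer to a classification flowchart with named inputs. That also stands. The flowchart could not be read here, so the discretion it leaves cannot be judged. No rule for resolving disagreement appears in the text.

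Third, a reader might infer more than the documents support:
- *That the adjudicators knew the arm.* The documents are silent. The open-label statement covers facilities, health workers and patients. Lack of masking is a reasonable inference, not a stated fact.
- *That mentors judged patients from their own clinics.* Nothing says so, and the number of mentors on the panel is not given.
- *That the five in the appendix are the seven less two mentors.* The composition of the five is not stated, so they may or may not include mentors.
- *That 46% against 56% shows bias.* The difference is compatible with chance, and Table S10's own test gives p=0.53.

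**Conclusion.** The point holds as a weakness in the design of outcome assessment, not as evidence of a biased result. A panel that includes the people who deliver the intervention decides part of the primary outcome, with no stated safeguard against knowledge of arm. The part that rests on probable calls is 12.9% of outcomes. The movement attributable to adjudication is about 1.1 crude points (-1.0 to +0.1), and moving the estimate by about 2 points would need roughly one in six probable calls in one arm (10 of 59 or 61) to be wrong in the same direction.

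These differences are crude: they ignore clustering and covariates. The +0.1 here should not be confused with the adjusted 0.1 in Table S12, which is a different quantity. Severity: should-fix. If the mentors did not in fact adjudicate, or the reviewers were masked, a clear statement to that effect would resolve most of the point.

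**What to change.** 1. State who adjudicated, whether they could see facility, wave or arm, and whether mentors handled cases from their own clinics. Reconcile seven members in the SAP with five in the appendix.
2. Exclude mentors and anyone else who delivered the intervention from the adjudication group.
3. Have the remaining existing members review files with facility, wave, arm and mentor notes removed and dates shown as time since enrolment. Write down the rule for disagreement.
4. Adjudication is complete and results by arm are tabulated. Re-adjudicate all 150 cases in this way, including the 30 definite failures, and report the result as a sensitivity analysis beside the pre-specified primary. Replacing the primary outcome now would change an endpoint after the results are known.

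The cost is the redaction of about 150 records and the reviewers' time. Sample size, alpha and power do not change, and no extra staff are needed, although how many members remain depends on the undocumented number of mentors. Masking may be imperfect where notes reveal the clinic, and members may remember cases they have already judged. Both limits should be reported with the result.

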## 2.0 Outcomes

### 2.1 Primary outcome

Treatment failure defined as a composite of any of the following:

- (1) Unsuppressed viral load (> 400 copies/ mL) 15 month after enrollment (window 11-19 months). We use the viral load measurement closest to 15 months of follow-up if multiple exist, or
- (2) documented disengagement in care (out of care during the 15-month follow up time point) if no viral load measurements are available, or
- (3) documented cessation or antiretroviral medication if no viral load is available, or
- (4) death at 15 months of follow up

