### **Objective 3: Evaluate the effect of the PCC intervention on retention and viral suppression.**

Ultimately, we seek to assess the effect of the targeted facility intervention on patient behaviors and clinical outcomes. We will use waves one and four of the stepped wedge design to evaluate the impact on retention and viral suppression. Our primary outcome will be retention, as measured by first episode of missing a clinic visit or drug pick up by 14 or more days. Secondary outcomes will be medication possession ratio, the “time in care” metric (defined as the fraction of time in care that the patient is late), time event analyses with longer intervals (30, 60 and 90 days) and viral load. The research team will support the facility to carryout routine monitoring and documentation of those results through existing data review meetings to strengthen facility performance as well as obtain crucial measurements to document intervention effects. In particular, as monitoring and evaluation systems have further expanded to capture engagement in community programs such as uptake of differentiated service delivery models, and the study will support existing efforts at the facilities to document clinical encounters, including those that happen outside of the facility.

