#### 8.7.2.2 Measurements of treatment failure

At a target of 15 months, we will assess treatment failure. We use 15 months for practical reasons. Although our original target was to assess treatment outcomes at 12 months, we instituted an additional three month period for ascertainment of viral load because 12 months after initial study start coincided with a period of health systems emergency in Zambia during the first wave of COVID-19 that made assessment of patient outcomes a challenge and also led to concomitant delay in study roll out (and extension of period two). We will accept data for a 15-month endpoint using information in at a minimum approximately a six month window around the 15-month point – recognizing that we will leverage and use clinically obtained viral loads when possible, and the timing of such measurements may or may not coincide with observation time in this study. Treatment failure is defined as a composite of (1) unsuppressed viral load ( $> 400$  copies/ mL), (2) documented disengagement in care, (3) switch of regimen for elevated viral load, or (4) death. We will treat documented prospective transfers to another facility as censored observations. For those who are traced and found to be transferred to another facility, if first visit is 14 or more days after last assigned return date at original clinic, patient will be considered a treatment failure, as well.

Viral load will be assessed using the Cobas CAP/CTM assay. We will collect baseline viral load from our cohort in wave 1. At the end of one year, we will check to see if patients have a viral load done in the course of routine clinical care in the correct window of time. If they do, then we will use that as the outcome value. If they do not, we will either encourage VL collection by clinic if clinical indications exist, or ask the participant to return to the facility and have their blood collected as part of the facility's routine collection. We will explore whether the facility has the capacity to collect samples in the field and will make use of that capacity if it exists. If this does not coincide with a routine clinical visit, the study will cover costs of transportation and time incurred by the

patient to have their viral load measured. We will use the viral load measurement closest to 15 months of follow-up if multiple exist.

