#### *8.7.2.1 Measurements for Retention*

For analyses using the full cohort of individuals in the EMR, we will assess retention using appointment and visits as recorded in the EMR.

### 8.8 Analysis for Objective 3

The primary outcome for objective 3 is treatment success 15 months after initial visit during period 1 of the study. For the analysis of this primary outcome we will assess the fraction with treatment success or not at 15 months using logistic regression. Random effects will be used to address within site correlation. Adjustment will be made for composition of the cohort recruited, in particular for age, sex, and time on ART at first visit during the study period. Sensitivity analyses for the primary analysis will include altering interval of absence considered a failure, and classifying all transfers out as either successes or failures.

For retention, we will calculate the cumulative incidence of a missed visit by 30 or more days at up until 15 months of follow-up time. We will use the Kaplan Meier approach, stratified by the intervention with a log rank test for significance. We will explore competing risks for transfers and mortality if those outcomes are not trivial in magnitude. In additional analyses we will use a multivariable regression, starting with Cox proportional hazards model if assumptions about data are met, to assess the effect of the intervention on retention. We will address clustering by site with a random effect term. In secondary analysis, we will adjust for facility and patient characteristics. If data are prevalent, we will consider the use of inverse probability weights or imputation to address missing outcomes.

### 8.9 Design of Objective 4

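### The SAP gives two outcomes for a death by month 15 after a suppressed viral load, and drops the protocol's transfer and regimen-switch rules without recording it

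*Combined protocol and SAP*

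**What the plan says.** **SAP (V3.1, February 2022).** Section 2.1 reads "Treatment failure defined as a composite of any of the following", followed by four components. The second (disengagement) and third (stopping antiretrovirals) count only if no viral load is available. The fourth is "4) death at 15 months of follow up", with no such limit.

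Under the outcome ascertainment process in 3.0, "Individuals with a documented suppressed viral load during the study outcome window (i.e., 11 to 19 months) are classified as" a definite success. The analysis text then counts definite and probable successes as successes. A patient without a viral load who is in care elsewhere, with a visit history showing unbroken engagement, is a probable success.

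**Protocol (version 1.5, January 2021).** Section 8.7.2.2 defines failure differently. Its last two components are "3) switch of regimen for elevated viral load, or (4) death". For documented transfers: "We will treat documented prospective transfers to another facility as censored observations". For traced transfers: "if first visit is 14 or more days after last assigned return date at original clinic, patient will be considered a treatment failure". Section 8.8 plans a sensitivity analysis that counts all transfers out as successes or all as failures.

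On the primary outcome, Objective 3 in protocol 5.1 says "Our primary outcome will be retention, as measured by first episode of missing a clinic visit" by 14 or more days, and 8.1.3 repeats this. Section 8.8 says "The primary outcome for objective 3 is treatment success 15 months after initial visit during period 1 of the study".

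**The concern.** A primary endpoint should give each patient one value under the written rules. Here a patient suppressed at month 12 who dies at month 14 has two. Following the SAP 3.0 classification literally would enter that death as a success.

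The protocol and SAP also differ on transfers and regimen switch, and neither says which governs. The supplement explains other departures, such as the changed missed-visit analysis in the Figure S6 legend, but not this one. A reader cannot tell a deliberate replacement from an omission, and the protocol's own check on transfers is no longer planned.

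**Working it through.** **1. Death.** SAP 2.1 limits components 2 and 3 to patients without a viral load but does not limit component 4. Death therefore overrides a viral load under 2.1. In 3.0 a suppressed value in the window is enough for definite success. The two conflict only when the suppressed value falls in months 11 to 15 and death follows by month 15. A death after month 15 is not clearly a failure under 2.1 either. Active tracing of vital status starts only when the window holds no viral load, so it does not reach these patients.

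A similar gap exists for stopping treatment: 3.0 makes clear documentation of not taking medication a definite failure, while 2.1 counts it only without a viral load. One order of precedence would settle both.

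**2. Transfers and switch.**
- Documented transfer: censored in protocol 8.7.2.2; no censoring in the SAP. Protocol 8.8 analyses a yes/no outcome at 15 months by logistic regression, where censoring has no defined meaning. Weighting or imputation appears there only as a possibility, in the retention paragraph, without mention of transfers.
- Traced transfer: failure in the protocol if 14 or more days late (a later paragraph says more than 14); no day limit in the SAP.
- Switch for elevated viral load: failure in the protocol; not mentioned in the SAP.
- All-success / all-failure run: in protocol 8.8; not in the SAP list.

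**3. Size.** Inputs, control / intervention:
- Suppressed in window (Table S12): 352/453 and 368/480.
- Probable successes without a viral load (Table S10): 27 and 34.
- Deaths (Table S11): 4 and 10.
- Silent transfers (S11): 16 and 7, of whom 15 and 7 had no endline viral load.
- Official transfers (S11): 35 and 39, of whom 11 and 10 had no endline viral load.

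Crude adjudicated success: (352 + 27)/453 = 83.7% and (368 + 34)/480 = 83.8%, a difference of +0.1 points. These are unadjusted; the plan's estimate comes from an adjusted mixed model.

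*Deaths.* If all 14 had been counted as successes and became failures: 375/453 = 82.8% and 392/480 = 81.7%, a difference of −1.1. The shift is 10/480 − 4/453 = 2.1 − 0.9 = 1.2 points against the intervention. That is the maximum if the same share of deaths is affected in each arm. If only one arm's deaths were affected, the shift would lie between −2.1 (10/480) and +0.9 (4/453).

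*Silent transfers.* If all 23 had been successes and became failures: 363/453 = 80.1% and 395/480 = 82.3%, a difference of +2.2, so a shift of 16/453 − 7/480 = 3.5 − 1.5 = about 2.1 points. With only the 22 lacking a viral load it is 15/453 − 7/480 = 1.9. One-arm extremes are +3.5 and −1.5.

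*Official transfers removed.* Denominators become 418 and 441. If all had been successes: 344/418 = 82.3% and 363/441 = 82.3%, difference 0.0. If those with a viral load were successes and those without were failures: 355/418 = 84.9% and 373/441 = 84.6%, difference −0.3. Applying one assumption in one arm and the other in the other gives −2.6 to +2.3.

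*Reach of the SAP's existing runs.* Transfers total 23 + 74 = 97 of 933 (10.4%). Those without an endline viral load number 15 + 7 + 11 + 10 = 43. The two SAP runs that reclassify or drop probable outcomes can touch only these. The other 54, of whom 74 − 21 = 53 are official transfers, are untouched.

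*Regimen switch.* No count is given, so no size can be computed.

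**The case against.** The strongest reply is that SAP 2.1 can be read as governing. The analysis section defines the primary outcome by reference to it, and 3.0 claims only to characterise that outcome further. The death conflict arises from silence, and the adjudication flowchart, not shown in the text available, may deal with death. All 14 deaths could sit among the 30 definite failures without a viral load in Table S10 (14 control, 16 intervention), in which case nobody is affected. This stands as a limit on size. It does not remove the need to state precedence, because the written rule in 3.0 contains none.

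The SAP is also the later document, so its silence on transfers and switch may be a replacement and not a second live rule. That is plausible, but unrecorded. Its probable-outcome runs do cover transfers without a viral load, and Table S12 reports a missing-equals-failure version: 0.1 (−9.2 to 9.3). They do not reach the other 54.

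A reader might infer two stronger points that the documents do not support:
- *That transfers and switches are handled in opposite ways.* A traced transfer who arrives on time is not a failure for lateness in either document. Results reverse only for a late arrival judged continuously engaged. Regimen switch is dropped, not reversed. Official transfers are also balanced (7.7% and 8.1%, p = 0.82).
- *That the choice of primary outcome decides between a null and a positive trial.* The protocol's retention primary is a visit missed by 14 or more days, and no such result is reported. The retention result in Table S8, 5.9 (0.6 to 11.2), is being in care at 15 months, which the SAP defines with a 30-day limit. In the treatment-success cohort, Table S9 gives retention at 15 months as 2.0 (−5.3 to 9.3).

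**Conclusion.** The point holds in limited form. The SAP gives two values for a patient suppressed in months 11 to 15 who dies by month 15. The number of such patients is unknown, from 0 to 14 recorded deaths. The effect is at most about 1.2 points if both arms are affected in the same proportion, and it may be zero.

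The SAP drops the protocol's transfer and switch rules and the transfer sensitivity analysis without recording it. The silent-transfer rule is worth at most about 2 points on the same equal-share assumption. That upper figure requires every silent transfer to have been both a SAP success and 14 or more days late, and neither is documented. Even the one-arm extremes, −2.1 for deaths and +3.5 for silent transfers, lie inside the Table S12 interval, so nothing here shows that the reading of the primary result would change.

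The retention wording in protocol 5.1 and 8.1.3 conflicts with 8.8 and with SAP 2.1, and looks like text left over from an earlier plan. The defect is an endpoint that the written rules do not fully determine. It should be corrected because correction is cheap.

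**What to change.** 1. In SAP 2.1 and 3.0, state one order, consistent with the SAP's own composite: death by month 15 is failure whatever the viral load; otherwise the viral load closest to 15 months decides; otherwise adjudication. Check the 14 deaths against their viral-load dates and report how many were affected.
2. Record in a dated note that the SAP definition supersedes the protocol's transfer and regimen-switch rules, or reconcile the passages. Since results are already reported, a note is more workable than rewriting the protocol. If censoring of documented transfers is kept, say how the logistic model handles it.
3. Restore the protocol's sensitivity analysis with all transfers counted as successes and then all as failures, covering all 97.
4. Reconcile protocol 5.1 and 8.1.3 with the single primary outcome of treatment failure/success at 15 months.

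The cost is wording, a look-up of 14 records and one extra sensitivity run on existing data.
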